### Randomization and allocation concealment

Eligible participants will be randomized with a 1:1:1 allocation ratio to receive the interventions. Randomization will be conducted by a blinded member of the research team using random permuted blocks stratified according to the history of PD-related infections (exit-site/tunnel infection or peritonitis) and the study setting. A list of numbers will be generated by copyrighted software (available at http://www.randomizer.org). The randomization blocks will be blinded to the investigators. Each study setting will be concealed using opaque envelopes opened only upon recruitment of an individual consented participant.

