**Methods/Designs:**

This study is a randomized, double-blind, multicenter, active-controlled, clinical trial. Adult patients aged 18 years or older who have end-stage kidney disease and are undergoing PD will be enrolled at three PD Centers in Thailand. A total of 354 PD patients will be randomly assigned to either the 2% chlorhexidine gluconate-impregnated patch, mupirocin ointment, or usual exit-site care with normal saline dressing according to a computer-generated random allocation sequence. Participants will be followed until discontinuation of PD or completion of 24 months. The primary study outcomes are time to first PD-related infection (exit-site/tunnel infection or peritonitis) event and the overall difference in PD-related infection rates between study arms. Secondary study outcomes will include (i) the rate of infection-related catheter removal and PD technique failure, (ii) rate of nasal and exit-site *Staphylococcus aureus* colonization, (iii) healthcare costs, and (iv) skin reactions and adverse events. We plan to conduct a cost-utility analysis alongside the trial from the perspectives of patients and society. A Markov simulation model will be used to estimate the total cost and health outcome in terms of quality-adjusted life years (QALYs) over a 20-year time horizon. An incremental cost-effectiveness ratio in Thai Baht and U.S. dollars per QALYs gained will be illustrated. A series of probabilistic sensitivity analyses will be conducted to assess the robustness of the cost-utility analysis findings.

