#### Statistical analysis

Baseline characteristics will be summarized as number (percentage) or mean ± standard deviation, or medians with interquartile range as suitable. Differences between treatment groups will be compared using Fisher’s exact test and analysis of covariance (ANCOVA) or Kruskal-Wallis test for categorical and continuous variables, respectively. All analyses will be conducted on both a per-protocol and intention-to-treat basis. All analyses will be performed using Stata software version 14.0 (StataCorp, LP) and Microsoft Excel version 2016. They will be two-tailed, and a *P*-value less than 0.05 will be considered statistically significant.

For a primary analysis, Cox proportional hazards regression and Poisson regression analyses will be performed to assess the effectiveness of the chlorhexidine gluconate-impregnated patch and mupirocin ointment compared to usual exit-site care with normal saline for the first episode of PD-related infection and longitudinal rates, respectively. Secondary analysis using statistical methods as described above will then be analyzed to evaluate the effect on the prevention of PD-related infections between chlorhexidine gluconate-impregnated patch and mupirocin ointment. The treatment effects will be estimated as hazard ratios or incidence rate ratios with corresponding 95% confidence interval. Kaplan-Meier survival curves will be constructed for visual presentation of time-to-event comparisons.

Several a priori subgroup analyses with respect to the minimization variables for both primary and secondary outcomes will be investigated. For instance, the lists of variables include age (<65 vs. ≥65 years), gender, history of diabetes, history of PD-related infections (peritonitis or exit-site/tunnel infection), *S. aureus* colonization status (nasal or exit-site PD catheter), PD modality (continuous ambulatory peritoneal dialysis vs. automated peritoneal dialysis), PD vintage, and serum albumin (< 3.5 vs ≥3.5 mg/dL).

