To address robustness of the treatment effects, further sensitivity analyses of the primary analysis will be performed by (i) adjusting for the several baseline covariates that seem to affect the outcomes (age, history of diabetes, history of PD-related infections, *S. aureus* colonization status, PD modality, PD vintage, and serum albumin); (ii) restricting the analysis to only PD-related infection episodes with positive cultures to account for misclassification bias; (iii) using the proportional sub-distribution hazards analyses by Fine and Gray method to address the completing risk outcomes, including mode switching to long-term hemodialysis, kidney transplantation, conservative treatment, or death; and (iv) using the multiple imputation method to evaluate the effect estimates when missing data are indicated.

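### The primary Cox and Poisson models name neither stratification factor, and study setting appears in no stated analysis; if the strata are prognostic, this costs power in the Cox analysis.

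*Protocol article*

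**What the plan says.** The section on randomization and allocation concealment describes "random permuted blocks stratified according to the history of PD-related infections (exit-site/tunnel infection or peritonitis) and the study setting". With three centres ("will be enrolled at three PD Centers in Thailand"), and history recorded as yes or no (an assumption), this gives six strata.

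The Statistical analysis section then states: "For a primary analysis, Cox proportional hazards regression and Poisson regression analyses will be performed". It gives the comparisons and the effect measures but no covariate, stratum or centre term. Further on, it lists sensitivity analyses of the primary analysis. The first is "adjusting for the several baseline covariates that seem to affect the outcomes", with the covariates written out. The list starts with "age, history of diabetes, history of PD-related infections", continues with *S. aureus* status, and ends with "PD modality, PD vintage, and serum albumin". Infection history is in it and study setting is not.

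The same section plans "subgroup analyses with respect to the minimization variables", although the design uses stratified blocks and not minimization. The variables it then offers as examples include infection history but, again, not study setting.

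**The concern.** Blocking within strata makes the arms alike on the stratifying factors. If those factors predict infection, the treatment estimate varies less between trials than an analysis ignoring them assumes. A Cox model has a second problem: leaving out a prognostic factor moves the hazard ratio toward 1 even when the arms are perfectly balanced.

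Both factors could plausibly matter here. The protocol itself counts infection history among covariates that appear to influence outcome. The centres are a large northern PD programme and two university hospitals in different regions, and the Discussion describes variation between facilities in exit-site prophylaxis.

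At stake is power for time to first infection, one of the two primary outcomes. There is also a reporting risk: adjusted and unadjusted results could differ with no stated reason to prefer the one that matches the design.

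**Working it through.** **The protocol's own figure.** It gives none for the effect of stratification. Its 118 per group serves here only as an input. That figure is reproduced by treating 0.70 and 0.49 as proportions with a continuity correction (94 per group) and multiplying by 1.25: 94 × 1.25 = 117.5, rounded up to 118. Whether that method is sound is a separate matter.

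**Inputs from the protocol.** Control rate 0.70 per patient-year, ratio 0.70, two-sided 5% level, 24 months of follow-up, 25% dropout, 118 per arm.

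**Assumptions, because the documents are silent.** 40% of patients have an infection history. Centre shares are one half, one quarter and one quarter. History multiplies the rate by 1.5, 2 or 3. One centre lies above the reference and one below it by a factor of 1.25, 1.5 or 2. These pairs are called weak, moderate and strong. Dropout is exponential.

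**Method.** 1,500 simulated two-arm trials per scenario, balanced within the six strata. Each trial was analysed without the factors, with both as covariates and, for Cox, also stratified by both. Monte Carlo standard error is √(0.5 × 0.5 / 1500) = 1.3 points near 50% power and √(0.05 × 0.95 / 1500) = 0.6 points near 5%.

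**Cox, time to first infection**

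| Strata | Mean HR without / with covariates | Power without | Power with covariates | Power stratified | Type I error without | Mean SE / true SD without, no effect |
|---|---|---|---|---|---|---|
| Weak | 0.707 / 0.697 | 52.5% | 54.7% (+2.2) | 53.5% (+1.0) | 5.1% | 0.1605 / 0.1593 = 1.01 |
| Moderate | 0.720 / 0.699 | 47.7% | 53.9% (+6.2) | 52.5% (+4.8) | 3.5% | 0.1637 / 0.1538 = 1.06 |
| Strong | 0.744 / 0.698 | 35.7% | 52.1% (+16.4) | 49.5% (+13.8) | 1.9% | 0.1714 / 0.1458 = 1.18 |

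With the covariates, type I error was 5.6%, 4.4% and 4.1%.

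**Where the Cox gain comes from.** In the moderate case at a true ratio of 0.70, the reported standard error does not shrink: 0.1724 without the factors, 0.1733 with them. The estimate moves instead. The typical test statistic is |ln 0.720| / 0.1724 = 1.91 without the factors and |ln 0.699| / 0.1733 = 2.07 with them, on either side of the 1.96 threshold.

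**Poisson, model-based standard errors.** Power without and with the factors was 77.5% and 77.9% (weak), 79.3% and 79.3% (moderate), 77.9% and 78.0% (strong). The standard error was 0.131 throughout, and type I error stayed near 5%.

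**Poisson, robust standard errors (not specified in the protocol).** Power went from 75.7% to 78.4%, from 71.7% to 80.3% and from 57.3% to 79.3%.

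**Extra variation between patients** (gamma variance 0.5, moderate strata). Model-based Poisson intervals become too narrow: with no effect, mean SE 0.119 against a true SD of 0.161. Type I error is 13.6% without the factors and 13.5% with them. The Cox gain falls to 3.5 points (35.4% to 38.9%).

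**A second set of assumptions** (3,000 trials, half with a history, history ratio 2, centre multipliers 1, 1.5 and 0.7). Log-rank power was 48.4%, and 53.6% when stratified. With a history ratio of 1.5 and no centre effect it was 55.8% and 56.1%.

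**The case against.** **The model terms may be in the SAP.** The article never says that the primary models are unadjusted, and exact terms are often left to a SAP. This stands in part: the unadjusted reading is an inference. But the article does state an adjustment policy. It places adjustment for infection history in a sensitivity analysis, which would be redundant if that factor were already in the primary models. For study setting the inference is weaker, since its absence from a list of additional covariates could mean that it is already a design term. Nothing in the text says so.

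**The Cox effect depends on assumed inputs.** This stands. With weak strata the gain of 1 to 2 points is close to simulation error, and the second set of assumptions has a case with almost none.

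**The hazard ratio changes meaning.** This also stands. The shift from 0.720 to 0.699 is the difference between a marginal and a conditional hazard ratio, not a bias removed at no cost.

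**Stronger readings that do not hold.** A reader might infer that both primary analyses lose power and give intervals that are too wide. For Poisson regression as written, the simulations show neither; with overdispersion its intervals err in the opposite direction. A reader might also infer that infection history is ignored altogether, but it is in the first sensitivity analysis and among the subgroup variables. Nor does the omission inflate false positives in the Cox test: its error is on the conservative side.

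**Conclusion.** The mismatch between design and analysis is in the text. The primary models as printed do not carry the factors used to restrict randomisation, and study setting is named in no analysis.

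The consequence is limited to the Cox analysis and is conditional on prognostic strata. It ranges from negligible with weak strata to a loss of 14 to 16 points of power with strong ones, with about 5 to 6 points in the moderate case. Confidence is high on the wording and low on the size, because the protocol gives neither the stratum effects nor the share of patients with an infection history. For the rate analysis, including the factors is a matter of consistency with the design. It should not be expected to add power under model-based standard errors or to deal with overdispersion.

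**What to change.** - Stratify the primary Cox model by infection history and study setting, or include both as covariates. State which. Covariates gave slightly more power in these simulations.
- Include both as fixed effects in the primary rate model.
- Add study setting to the covariate list of the adjusted sensitivity analysis.
- Report the unadjusted results as supportive, and say that the adjusted hazard ratio is conditional on the strata.
- Replace the reference to minimization with wording that matches the stratified blocks.

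The cost is a few lines of text. Both factors are known for every participant at randomisation, and the sample size is unchanged. Averaged over six strata, 354 participants give 59 per stratum, or about 20 per arm, so stratification is workable unless one stratum turns out very small. The one real cost is the conditional interpretation. The Trial status section reports enrolment still open, with 288 randomised by July 2019, so on that status the change could be made before unblinding.

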### Blinding

In the COSMO-PD trial, participants and their caregivers, physician, PD nurse, and all staff members at the study site will be blinded. Based on the blinding method, the outcomes of interest and statistical analysis will be assessed by a third-party not participating in recruitment or treatment follow-up. Unblinding will be permitted in cases of serious adverse event or in emergencies that affect optimal treatment care. The investigators will be unblinded only at the end of the study.

Regardless of their study arm allocation, participants will receive a set of two identical ointment tube (either IMPs or placebo) and a plastic nonionized patch sachet (either IMPs or placebo) with directions for use. The study intervention drugs will be administered by nursing staff at each study site. Physicians will access participant eligibility, obtain consent, recruit participants, care for participants during the study, collect data, and assess outcomes.

To examine our blinding procedures, we conducted a pilot study between June 2016 and August 2016 and enrolled 30 pilot participants at two study settings (Nakornping Hospital and Maharaj Nakorn Chiang Mai Hospital). No change was made to the study protocol interventions or administration based on this pilot study. After completion of the pilot study ensuring feasibility of the IMPs process and study flow in August 2016, the actual COSMO-PD trial enrollment was initiated in September 2016.

### Participants’ timeline and assessment

Participants will be assessed every 3 months from baseline to 24 months alongside routine outpatient PD clinic visits as per the trial schedule for assessment (Table 3). During the assessment period, participants and their assisted caregivers (if available) will be screened for nasal and PD catheter exit-site *S. aureus* colonization. Sociodemographic data (e.g., age gender, smoking and alcohol drinking status, weight, height, PD vintage, cause of ESKD, residual urine volume, dialysate adequacy, and routine laboratory tests) and details of medical history and medications will be gathered at baseline. Dialysate characteristics and exit-site assessment, using Twardowski and Prowants’ classification system [28], will be assessed at each visit as well as adverse events and skin reactions.

**Table 3 Tab3:** Schedule of observation and procedures

Parameter	Study period: time (month)											
	Screening	Assessment and follow-up									Close-out	
	-1	0	3	6	9	12	15	18	21	24	25	26
Check eligibility against inclusion/exclusion criteria and medication review	X											
Screening for *S. aureus* colonization	X			X		X		X		X		
Gartering informed consent and randomization		X										
Sociodemographic and lifestyle data^a^		X										
Medical history by Charlson comorbidity index and ESKD etiology		X										
Physical examination	X	X	X	X	X	X	X	X	X	X		
PD-related infection: dialysate characteristics and exit-site assessment		X	X	X	X	X	X	X	X	X		
Routine laboratory tests (performed locally)^b^		X	X	X	X	X	X	X	X	X		
Dialysate adequacy and peritoneal equilibration test		X				X				X		
HRQOL and mental health^c^		X		X		X		X		X		
Record medication changes		X	X	X	X	X	X	X	X	X		
Safety profiles: skin reactions and adverse events documentation		X	X	X	X	X	X	X	X	X	X	
Hospitalization and emergency visit		X	X	X	X	X	X	X	X	X		
Assess adherence with trial treatment allocation and other medication^d^			X	X	X	X	X	X	X	X		
Healthcare costs: direct medical cost, direct non-medical cost, and indirect cost		X				X				X		
Data monitoring			X	X	X	X	X	X	X	X		
Statistical analysis and reporting											X	X

^a^To include date of birth, date of PD initiation, gender, weight, body mass index, marital status, education, income, insurance, smoking and alcohol status

^b^To include complete blood count, biochemistry, liver function test, and dialysate profile parameter

^c^To include the Kidney Disease Quality of Life-36, EuroQol-5 dimension-5 level, and BDI-II, Beck Depression Inventory-II questionnaires

^d^To include the visual analog scale-medication adherence and the medication-taking behavior measure for Thai patients questionnaires

Abbreviations: *ESKD* end-stage kidney disease, *HRQOL* health-related quality of life, *PD* peritoneal dialysis, *S. aureus Staphylococcus aureus*

### Outcomes

#### Primary outcome

The primary outcomes of the COSMO-PD trial are time-to-first PD-related infection (exit-site/tunnel infection or peritonitis) event and overall difference in PD-related infection rates between study arms. PD-related peritonitis and exit-site/tunnel infection will be defined according to the ISPD guidelines [2, 7]. Participants will be diagnosed as having peritonitis if they meet at least two of the following criteria: (i) clinical features (e.g., abdominal pain and/or cloudy dialysis effluent); (ii) dialysate effluent white cell count more than 100 cell/μL (after a dwell time of at least 2 h), with polymorphonuclears making up more than 50%; and (iii) positive dialysis effluent culture. Exit-site infection and tunnel infection will be indicated as the presence of purulent discharge (with or without erythema of the skin) and evidence of collection along the catheter tunnel (clinical inflammation or ultrasonographic), respectively.

#### Secondary outcomes

Secondary outcomes include the following:

*Clinical events*
Infection-related catheter removalPD technique failure

*S. aureus colonization*
Incidence of nasal *S. aureus* colonizationIncidence of exit-site *S. aureus* colonization

*Healthcare costs*
Direct medical costs including for the IMPs, non-IMPs and equipment, outpatient and emergency visits, hospitalization, antimicrobial treatment for PD-related infection, laboratory tests and procedures, and costs related to adverse eventsDirect non-medical costs including for transportation and the monetary value of informal careIndirect costs including daily wages of participant and family caregiver for treatment follow-ups and extra visits

*Safety*
Skin reactionsSafety of IMPs related to potential harm (e.g., adverse events, serious adverse events, participant survival in each group, hospitalization, and emergency visits)

#### Additional outcomes

Additional outcomes include the following:

*Health-related quality of life*
Kidney Disease Quality of Life-36, which is a kidney-specific quality-of-life instrument that explores generic core plus burden of kidney disease, symptoms/problems of kidney disease, and effects of kidney disease scales [29]EuroQol-5 dimension-5 level (EQ-5D-5 L), which is a 5-level assessment of mobility, self-care, usual activities, pain/discomfort, anxiety/depression, and the visual analog scale [30]

*Depressive symptoms*
Beck Depression Inventory-II, which is a 21-item self-reporting questionnaire for evaluating the severity of depression in normal and psychiatric populations [31]

*Medication adherence*
Direct observation and recording of the use of IMPs via return plastic sachets and ointment tubesGlobal rating of medication adherence by the visual analog scale, where the self-reported adherence level is illustrated with a 10-cm line, where 0 represents “non-adherence—none of the medications taken” and 10 represents “good adherence—every single medication consistently taken”Medication-taking behavior measure for Thai patients, which includes a 6-item assessment of mediation-taking behaviors among Thai patients with chronic diseases [32]

### Safety monitoring and trial-related injury

The independent multidisciplinary Data Safety Monitoring Board (DSMB) will be assembled to oversee the study in terms of monitoring and evaluating safety and trial-related injury. Any adverse event needs to be documented in detail, including information on the starting point of symptoms, participant symptoms, severity, duration of the condition, any management administered, final outcome, and relationship with the IMPs among others. In the case of a serious adverse event, the investigator is responsible for informing the DSMB and contacting the statistician to obtain the participant’s allocation information immediately after he/she has established the event.

Additionally, skin reactions will be closely monitored, and participants will be asked to shade the parts of the body to scale if involved. The skin-related event will be classified into Grade I (faint macular erythema [redness] only), Grade II (erythema, edema, and possibly papules), Grade III (erythema, edema, papules, and blisters), and Grade IV (blisters and ulceration [skin breakdown]).

No clinical trial insurance will be provided, and participants will not receive financial compensation for any trial-related injury. However, participants will receive full access to outpatient and in-hospital standard of care.

### Study auditing

A clinical monitor will visit the study sites every 2 weeks to check the progress of the study. Important points to be checked include whether the investigator has conducted the study as per protocol, how many participants were screened and enrolled, and if all eligible participants signed the informed consent form. Completeness of case report form and other essential documents, as well as records of any drop-outs or adverse events, will be checked for correctness and consistency with the source documents in a timely manner.

### Statistical analysis plan

#### Sample size and power calculations

Sample size calculation was based on information from the Thai Renal Outcomes Research-Peritoneal Dialysis database collected between 2006 and 2016, with an estimated rate of 0.31 episodes per patient-year and 0.39 episodes per patient-year for exit-site infection and peritonitis, respectively (composite rate of PD-related infections of 0.70 episodes per patient-year) [3]. To detect an expected clinically relevant difference in both exit-site infection and peritonitis rate of 30% (0.70 episodes per patient-year vs. 0.49 episodes per patient-year) between our usual exit-site care with normal saline and interventions (either chlorhexidine gluconate-impregnated patch or mupirocin ointment), approximately 118 participants per group will be enrolled to obtain 80% power with a two-sided significance level of 0.05, while allowing for 25% all-cause dropout during the study period. Thus, the overall targeted minimum sample size will be 354 participants.

